### Interventions

This randomized clinical trial will have two groups, namely, the reflex locomotion group and the Bobath concept group.

The therapies will be described following the recommendations of TIDieR (27) (template for intervention description and replication checklist).

#### Reflex locomotion group

**Brief name:** Reflex Locomotion.

**Why:** Reflex locomotion contains two patterns of global movements, namely, reflex crawling, which is triggered from the prone position, and the turning reflex, which is triggered from the lying down supine and lateral positions. These two patterns are called coordination complexes. Both are innately present in the functioning of the CNS.

Activation of coordination complex muscles that occur in reflex locomotion is generated by touch and proprioception elicited by the hands of the therapist in some specific areas or activation points, and some vector directions are established. Trigger points can be stimulated individually or in combination; by doing so, the latter form would generate a greater input to the CNS and would increase the benefits for the activation of gait patterns. “The kinesiological character on Reflex Locomotion contains essential elements in locomotion, among those that include postural adjustment, straightening on a point of support and the coordinated phasic movement.”

**What (materials):** The only material necessary for the application of reflex locomotion will be a stretcher or floor mats on which the patient will be supported while the physiotherapist applies the intervention.

**What (procedures):** For the application of reflex locomotion therapy, stimulation will be used in the chest area following the pattern of the flip reflex locomotion complex (RV) in its first phase. To do this, the subject will be placed in a supine position aligned with respect to the axial axis, with the arms along the body, the lower extremities extended, and the head extended with a rotation of ~30° to one side of the stimulation. A stimulation pressure between 1.4 and 1.8 kg/cm^2^ ± 200 g will be exerted in the space between the 6th and 7th or 7th and 8th ribs below the mammillary line. Individuals will also be placed in the reflex crawling (RR) position with the patient in the prone position and the head turned 30°. They will be stimulated in the calcaneus area with the same pressure as in the first phase of the reflex rollover. Figure 1 shows the treatment according to Vojta's reflex locomotion. In our study, the starting position of the patient can be modified depending on the degree of mobility and spasticity that the patient may present.

**Figure 1 F1:**
[figure not shown]
Neurorehabilitation treatment according to Vojta's reflex locomotion.

**Who will provide:** All interventions will be performed by a physiotherapist with more than 20 years of experience in treating people with neurological problems.

**How:** The physiotherapy technique will be performed individually twice a week for a duration of 45 min for a period of 12 months (22, 23).

**Where:** All sessions will be conducted at the Faculty of Nursing and Physiotherapy, University of Salamanca (Spain).

**When and for how long:** Participants will receive two sessions per week for 12 months. The average duration of the session will be ~45 min. The same weekly schedule will always be respected for each of the participating subjects.

**Tailoring**: Due to the nature of the intervention and the wide heterogeneity of the subjects, the sessions will be individualized and tailored to each subject.

**How well (planned):** Therapy supervision will be provided through weekly meetings between therapists and investigators. In addition, a thorough control of the subjects' attendance at the sessions will be carried out.

**How well (actual):** Not applicable.

#### Bobath concept group

**Brief name:** Bobath Concept.

**Why:** The Bobath concept is a therapeutic approach used in the rehabilitation of people with neuromotor disorders based on brain plasticity, normal motor control, typical motor development, biomechanical analysis, facilitation and inhibition, and a holistic approach to neuromotor disorders. Its main goal is to improve motor function and promote the person's active participation in his or her environment.

**What (materials):** To apply Bobath therapy, a variety of materials and equipment are required to help the therapist facilitate and promote motor function in people with neuromotor disorders. These include mats, therapeutic balls, mirrors, parallel bars, balance cushions, elastic bands, and pulleys. It is important to note that the materials and equipment used may vary depending on the specific needs of each patient.

**What (procedures):** For the application of the Bobath concept, different postures will be applied to inhibit tone and abnormal movement patterns, facilitate normal movement, and stimulate muscular inactivity. To this end, pathological coordination patterns controlled by tonic activity (tonic reflexes) will be inhibited by controlling specific points. It will also facilitate normal coordination patterns controlled by straightening and balancing reactions. It will activate weak muscle groups in the trunk and in the lower and upper limbs to increase muscle tone. To do this, a precise stroke is performed with the therapist's outstretched fingers along the extension of the muscle or a number of muscles working in the same direction. Figure 2 shows the treatment according to the Bobath concept.

**Figure 2 F2:**
[figure not shown]
Neurorehabilitation treatment according to the Bobath therapy.

**Who will provide:** All interventions will be performed by a physiotherapist with more than 20 years of experience in treating people with neurological problems.

**How:** The physiotherapy technique will be performed individually twice a week for a duration of 45 min for a period of 12 months.

**Where:** All sessions will be conducted at the Faculty of Nursing and Physiotherapy, University of Salamanca (Spain).

**When and for how long:** Participants will receive two sessions per week for 12 months. The average duration of the session will be ~45 min. The same weekly schedule will always be respected for each of the participating subjects.

**Tailoring**: Due to the nature of the intervention and the wide heterogeneity of the subjects, the sessions will be individualized and tailored to each subject.

**How well (planned):** Therapy supervision will be provided through weekly meetings between therapists and investigators. In addition, a thorough control of the subjects' attendance at the sessions will be carried out.

**How well (actual):** Not applicable.

**Extraction of samples:** Tear samples from MS patients will be collected at the Institute of Neurosciences of Castilla y León. For this, tears will be collected on graduated Schirmer's strips, as previously described by Pieragostino et al. (28). The Schirmer's test will be purchased from Praxisdienst GmbH & Co KG (Longuich, Germany), and the strips will be gently placed on the lower eyelid. Since the strips are graduated, they will be kept on the lower eyelid until the signal reaches the indicated mark. Subsequently, the strip will be placed in a 2.0-ml Eppendorf tube and stored at −80°C until further analysis. Figure 3 shows an example of tear extraction.

**Figure 3 F3:**
[figure not shown]
Schirmer's test uses paper strips placed in the lower eyelid, and its score is determined by the length of the moistened area of the strips (using the scale packaged with the strips). Tears are usually collected until the patient's eyelid normally moistens 20 mm of each paper strip.

### Sample analysis

Lipids will be extracted from paper strips moistened with the patient's tears. To this end, a modified method of Bligh as described by Hijazi et al. (29) will be used. Briefly, the samples will be extracted with chloroform-methanol-water (2:1:1, in vol.) and mixed with corresponding internal standards (heptadecanoic acid for lipid analysis and protein calibration standard I (Bruker Daltonics) for proteomic analysis). After centrifugation at 2,000 × *g* for 15 min at 4°C, the resulting organic phase, the interphase, and the aqueous phase will be isolated.

The organic layer will be evaporated to dryness under a nitrogen stream. The final residue will be resuspended in a solution of methanol-chloroform (2:1, v/v) to a concentration higher than 5 pmol/ml and then analyzed directly in the chromatograph. The concentration of fatty acids in the sample will be determined in a Waters Acquity UPLC™ H-Class-Xevo TQS™ chromatograph coupled to a triple quadrupole mass spectrometer [LC-MS/MS(QqQ)], which allows performing nominal mass and is available at the General Mass Spectrometry Service (Nucleus) of the University of Salamanca. Different commercial fatty acid standards will be used to determine the retention time of each fatty acid.

The aqueous and interphase phases will be evaporated to dryness in a Speedvac and resuspended in 2.5% ACN and 50% TFA for protein detection using MALDI-TOF-TOF (matrix-assisted laser desorption/ionization time of light) AutoFlex mass spectrometry III of the Proteomics Unit of the Biomedical Research Institute of Neurosciences of Castilla y León. For automated data analysis, the obtained spectra will be processed using the MALDI Biotyper 3.0 program (Bruker Daltonics GMbH, Leipzig, Germany).

### Outcomes

In the baseline assessment, all variables, including sociodemographic variables, will be measured. Subsequently, all outcome variables will be measured at 3, 6, and 12 months and coded by a person external to the intervention.

Personal and sociodemographic variables are as follows:

Age (years).Sex (male or female).Weight (kg), height (m), body mass index (BMI; kg/m^2^).Study level (no studies, basic education, secondary school, or superior studies).Marital status (single, married, separated, divorced, or widowed).Time since diagnosis of MS (years and months).Smoking (yes or no).Pharmacological treatment (name and number of pills per day).Comorbidities (name).

#### Primary outcome variables

The primary outcome measures are respiratory function, balance, spasticity, reaction time, and quantification of lipid biomarkers. Figure 4 shows the timeline of the intervention and the evaluations of the different variables.

**Respiratory function:** Maximum inspiratory pressure (PIMax) is the maximum pressure generated by the inspiratory muscles when performing a forced inspiration; in practice, it is a simple and global evaluation of the strength of the inspiratory musculature. Its knowledge is of great importance since it allows us to compare it with published reference values, use it in the programming of inspiratory training, and check its evolution over time, thus assessing the effectiveness of a respiratory rehabilitation program or inspiratory training (30). PiMax will be measured with the Baluue peak flow meter inspirometer.**Balance:** The Berg Balance Scale was developed in 1989 to measure balance in the elderly (31). The scale consists of 14 items, scored from 0 to 4, which are added to make a total score between 0 and 56; a higher score indicates better balance. The items vary in difficulty, from sitting in a chair to standing on one leg. The Berg Balance Scale takes ~10–15 min to complete. It requires a chair, a stopwatch, a ruler, and a step. Although the Berg Balance Scale was originally developed to measure balance in the elderly, it is now commonly used to measure balance in people with varying conditions and disabilities (32).**Spasticity:** The Tardieu scale has been suggested as a better instrument for classifying spasticity because it uses slow and fast speeds in accordance with the definition of spasticity and can differentiate between neural and biomechanical contributions to resistance to passive movement (33–35).**Reaction time**: Reaction time refers to the amount of time that elapses from when we perceive something until we respond accordingly. Therefore, it is the ability to detect, process, and respond to a stimulus. Any type of disorder that involves perception, information processing, or motor problems will affect reaction time. Therefore, response time is a cognitive ability that is very sensitive to alterations. Reaction time will be measured through the CogniFit program (36). CogniFit is a computerized cognitive training program that was found to be effective in improving reaction time and cognition (37, 38).**Lipid biomarkers**: Cicalini et al. (24) analyzed the lipid profile of 30 different phospholipids using lipidomics, resulting in a significantly lower concentration of sphingomyelin in subjects with MS. In this study, in addition to analyzing the amount of sphingomyelin, we will analyze phospholipids such as phosphatidylcholine, phosphatidylserine, phosphatidylethanolamine, and free fatty acids such as arachidonic acid, arachidic acid, and linoleic acid. The objective of analyzing these lipids plus sphingomyelin relies on their predominance in cell membranes and myelin sheaths, which are involved in MS pathology.

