### Power and sample size

The sample size was calculated using the G^*^power Software (version 3.1.7), resulting in a minimum of 54 participants for the development of the study. The estimated effect size for the main outcome measures established in this study was 0.25. A power of the statistical test of 0.95, an alpha error of 0.05, a correlation between repeated measurements of 0.5 (two groups, two measurements), a sphericity correction coefficient of 1, and a loss percentage of 20% are taken into account.

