### Statistical methods

Statistical analysis will be performed using the SPSS 27.0 statistical software for Windows (SPSS Inc., Chicago, IL; version 27.0). The normality of the sample will be checked using the Shapiro-Wilk test, and if it follows a normal distribution, an analysis of variance (ANOVA) of repeated measures *p* will be used, with time (pre-treatment and post-treatment) as an intra-group factor and Vojta and Bobath groups as the inter-group factor, all with a Bonferroni correction. Statistical analysis will be performed with a confidence level of 95%, so a *p*-value of < 0.05 will be considered significant values.

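### Five primary outcome domains have no success rule, and the sample size uses an undivided alpha of 0.05: either the family-wise error is uncontrolled or the stated power of 0.95 is not met

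*Protocol article*

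**What the plan says.** - **Primary outcome variables:** "The primary outcome measures are respiratory function, balance, spasticity, reaction time, and quantification of lipid biomarkers". No domain is ranked above another, and nothing says whether one, some or all must favour reflex locomotion. Within the lipid domain, besides sphingomyelin, the text says "we will analyze phospholipids such as phosphatidylcholine, phosphatidylserine, phosphatidylethanolamine, and free fatty acids such as arachidonic acid, arachidic acid, and linoleic acid". That makes seven named analytes in an open-ended list.
- **Power and sample size:** one calculation serves all of these outcomes: "The estimated effect size for the main outcome measures established in this study was 0.25". The error rates are "A power of the statistical test of 0.95, an alpha error of 0.05". The other inputs are a correlation of 0.5, two groups, two measurements and a sphericity coefficient of 1. The result is 54 participants.
- **Statistical methods:** a repeated-measures ANOVA with a two-level time factor and a two-level group factor, "all with a Bonferroni correction", and significance at p < 0.05. The set of tests that the correction covers is not stated.
- **Hypotheses:** reflex locomotion is expected to improve physical condition and quality of life more than Bobath. Tear compounds are to monitor that improvement, and sphingomyelin is the only one named there.

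**The concern.** Five primary outcomes, a Bonferroni correction and one sample size calculation at "an alpha error of 0.05" have to fit together, and it is not clear that they do. The decisive question is which tests the correction covers. If it covers only comparisons inside each outcome's ANOVA, each domain is tested at 0.05 and nothing limits the chance of at least one false positive among them. If it covers the five domains, the sample size was computed at a more lenient alpha than the analysis will use.

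What counts as a positive trial is at stake. Without a decision rule, a report could rest a claim of superiority on whichever domain reached p < 0.05, or the trial could be described as having a power that it lacks.

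**Working it through.** **Inputs** (Power and sample size, unless noted): effect size 0.25, read as Cohen's f because that reading reproduces the stated N; alpha 0.05; power 0.95; correlation ρ = 0.5; g = 2 groups; m = 2 measurements; sphericity coefficient 1; N = 54. Number of primary domains: k = 5 (Primary outcome variables).

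**Step 1. Reproduce the plan's figure.** For the group-by-time interaction:

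λ = f² × N × m / (1 − ρ) = 0.0625 × 54 × 2 / 0.5 = 13.5, with 1 and N − 2 = 52 degrees of freedom.

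The noncentral F distribution gives power 0.9501 at alpha 0.05. At N = 52 power is 0.942, so 54 is the smallest even total that reaches 0.95. The stated figure reproduces with alpha undivided and leaves no allowance for several primaries.

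**Step 2. Reading A: the correction acts inside each ANOVA.** With two time levels and two groups, each factor has one pairwise comparison, so the correction multiplies p by 1. If the 3- and 6-month visits listed under Outcomes were added as time levels, there would be six pairwise time comparisons and the correction would have some effect, but still only within one outcome. Each domain is tested at 0.05, and under the global null:

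Family-wise error = 1 − 0.95⁵ = 0.226 if the tests are independent.

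The documents give no correlation between outcomes, so a range was simulated with equal pairwise correlation (two-sided normal tests):

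| Assumed correlation | Family-wise error, 5 domains |
|---|---|
| 0 | 0.23 |
| 0.3 | 0.21 |
| 0.5 | 0.18 |
| 0.8 | 0.13 |

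If, in addition, each of the seven named lipids were tested as its own primary, there would be 4 + 7 = 11 tests, and 1 − 0.95¹¹ = 0.431 under independence (about 0.30 at correlation 0.5).

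**Step 3. Reading B: the correction acts across the five domains.** Alpha per domain = 0.05 / 5 = 0.01. With the same λ = 13.5 and 1 and 52 degrees of freedom, power is 0.837. Power 0.95 at alpha 0.01 would need 76 evaluable participants.

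**Step 4. Reading C: all five must succeed.** No alpha adjustment is needed, but joint power under independence is 0.95⁵ = 0.774. Positive correlation raises this, but joint power cannot exceed the power of a single test, 0.95, and reaches it only if the five tests always agree.

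**The case against.** The strongest defence is that the protocol does not contradict itself. On reading A, alpha 0.05 in the sample size, the correction inside each ANOVA and the p < 0.05 threshold are mutually consistent. A reader might infer that one of these statements must be false. That does not follow. On reading A they agree, and what fails is error control across outcomes.

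Three further points limit the concern.

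- **The count of 11.** A reader might take the 43% as the headline. The article lists the lipids as one primary measure and does not call each analyte a primary. The Hypotheses section gives tear compounds a monitoring role. The supportable family is five domains, and 43% is an upper case that applies only if every named lipid is tested as primary.
- **Loss to follow-up.** A reader might quote power at about 43 completers (54 × 0.8 = 43.2). Power there is already 0.893 at alpha 0.05, so the lower figures at that size mix dropout with multiplicity. Whether 54 already includes the 20% loss is a separate point.
- **Co-primary outcomes in the strict sense.** If all five had to succeed, the family-wise error would not be inflated. The article neither uses that term nor states that rule, and it does not state that any one success is enough. Reading C covers this case, and the stated power still fails.

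It can also be said that the Bonferroni family belongs in an analysis plan that is not shown. That would answer a complaint about missing detail. But the article itself fixes the five primaries, the alpha, "A power of the statistical test of 0.95" and the sample size. A later document could choose reading B or C, but it could not make 0.95 the power of the corrected or joint test at N = 54.

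**Conclusion.** The concern holds for five domains. Followed as written, the plan gives one of three results:

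- a family-wise error of about 23% under independence (about 18% at correlation 0.5, and 13% even at 0.8);
- power of 0.84 per domain, if the correction spans the five domains;
- joint power of about 0.77 under independence, if all five must succeed.

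None of these delivers both 5% error control across the primaries and the stated 0.95. The wording under Statistical methods favours the first result, but the text does not settle it.

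The figures rest on the plan's own effect size and correlation between repeated measurements, on the group-by-time interaction as the deciding test, on one endpoint per domain, and on all 54 participants being analysed. The correlations between outcomes are assumptions.

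**What to change.** Before unblinding:

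1. State that the correction applies across the primary domains.
2. Name one endpoint per domain. For lipids, use sphingomyelin, the only lipid named in the Hypotheses section, and label the others exploratory.
3. Test the five between-group contrasts by Holm's procedure at family-wise 0.05.
4. Restate the power as about 0.84 per endpoint at alpha 0.01 and N = 54. Holm's first step uses 0.01 and later steps are more lenient, so this is a conservative figure for any one endpoint.

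Alternatively, name one domain as the sole primary, keep alpha 0.05 and the existing calculation, and make the other four secondary. Either scheme is acceptable, provided the choice is made without sight of results by group.

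The cost is a less favourable stated power under the first option, or the demotion of four outcomes under the second. Both need an update to the protocol and the registration. Neither needs further data.

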
**Figure 4 F4:**
[figure not shown]
Timeline.

### Power and sample size

The sample size was calculated using the G^*^power Software (version 3.1.7), resulting in a minimum of 54 participants for the development of the study. The estimated effect size for the main outcome measures established in this study was 0.25. A power of the statistical test of 0.95, an alpha error of 0.05, a correlation between repeated measurements of 0.5 (two groups, two measurements), a sphericity correction coefficient of 1, and a loss percentage of 20% are taken into account.

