**Methods and analysis:**

This is a randomized controlled trial on the effectiveness of two neurorehabilitation techniques in patients with multiple sclerosis conducted at the University of Salamanca. The research will take place at the Faculty of Nursing and Physiotherapy, University of Salamanca. The study will be conducted from June 2023 to June 2024. The reflex locomotion group will receive individual sessions of therapy (*n* = 27), and the Bobath concept group (*n* = 27) will receive the same number of sessions. Both groups will receive two sessions per week for 12 months. The measurement variables will be the Berg Balance Scale, the Tardieu Scale, the Cognitfit Program, Maximum Inspiratory Pressure, and Lacrimal Biomarkers.

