### Participants: inclusion/exclusion criteria

A total of 50 participants will be recruited from the general population with a diagnosis of multiple sclerosis according to the Expanded Disability Status Scale who attend their neurology consultation at the University Hospital of Salamanca. The participants in this study will be adults, aged between 20 and 60 years, of both sexes. All subjects will sign a written informed consent form before any data are collected.

Exclusion criteria will be as follows: (1) Participants with multiple sclerosis with an EDSS scale score equal to or higher than 7.0 will be excluded, (2) Pregnant women, (3) Oncology patients, (4) Non-acceptance and non-signing of the informed consent, (5) Refusal to participate in the study, (6) Patients with severe cognitive impairment that does not allow them to understand the development of the study, (7) Patients with cardiovascular instability, (8) Patients who do not complete at least 75% of the scheduled sessions, (9) Patients who do not present any of the contraindications contemplated for reflex locomotion.

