### Limitations

#### Risk factor 1: selection and number of patients

A total of 50 patients diagnosed with RRMS will be selected. They will come from Salamanca's capital and its province. Considering that the MS Care Unit of Salamanca Hospital evaluates more than 300 patients diagnosed with MS disease in general, an initial screening will be carried out to select 50 individuals who could benefit from these therapies. Individuals belonging to different MS associations from nearby provinces to Salamanca (Salamanca) may also participate if there is a need to select additional participants in this assay.

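### The 54 participants said to allow for 20% loss is exactly the no-loss sample size, and two sections recruit only 50

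*Protocol article*

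**What the plan says.** All references are to the protocol article.

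- **Power and sample size** reports a G*Power calculation "resulting in a minimum of 54 participants for the development of the study". The inputs are given in full: effect size 0.25, target power 0.95, alpha 0.05, measurements correlated at 0.5, two groups and two time points. The list ends with "a sphericity correction coefficient of 1, and a loss percentage of 20% are taken into account". The section does not name which repeated-measures test was chosen.
- **Abstract, Methods and analysis** gives 27 participants in each arm, so 54.
- **Participants: inclusion/exclusion criteria** says "A total of 50 participants will be recruited from the general population with a diagnosis of multiple sclerosis". Its exclusion list also removes anyone who completes less than 75% of the scheduled sessions.
- **Limitations, Risk factor 1** says "A total of 50 patients diagnosed with RRMS will be selected" and repeats 50 as the number to be selected at screening. It adds that people from MS associations may take part if more are needed.
- **Limitations, Risk factor 2** says that a new subject or a longer project may be considered after MS attacks.
- **Statistical methods** plans a repeated-measures ANOVA with time (pre and post) and group as factors.

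**The concern.** Two things do not fit together. First, a sample size that already allows for 20% loss should exceed the number needed for analysis, yet 54 looks like the direct software output for the listed inputs. Second, the recruitment target in two sections is lower than the minimum in the sample size section.

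What is at stake is the stated power. Treatment runs twice weekly for 12 months, and poor attenders are excluded, so some loss is to be expected; the authors themselves put it at 20%. If the allowance was never added, a null result would be read as coming from a trial with 95% power when the completed trial has less. The two recruitment figures also leave it unclear how many people will be enrolled.

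**Working it through.** **Inputs, all from Power and sample size:** f = 0.25, alpha = 0.05, target power = 0.95, k = 2 groups, m = 2 measurements, correlation ρ = 0.5, sphericity ε = 1, loss 20%.

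**Step 1: reproduce 54.** For the group-by-time test in G*Power's repeated-measures ANOVA with its default effect-size definition, power comes from a noncentral F distribution with

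- λ = f² × N × m × ε / (1 − ρ) = 0.0625 × N × 2 / 0.5 = 0.25 N
- df1 = (k − 1)(m − 1) = 1
- df2 = (N − k)(m − 1) = N − 2

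At N = 54, λ = 13.5 and power is 0.9501. At N = 53, λ = 13.25 and power is 0.9464. So 54 is the smallest N that reaches 0.95, with every participant evaluable.

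**Step 2: is the result specific to that test?** With two groups and two measurements, the within-factor (time) test has the same λ and the same degrees of freedom, so it also gives 54. The between-factor test needs 158, and the alternative effect-size convention (λ = f²N) needs 210. The two tests that give 54 both do so before any loss.

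**Step 3: add the stated loss.** 54 / (1 − 0.20) = 67.5, so 68. Multiplying by 1.2 instead, a common mistake, gives 64.8, so 65. Neither is 54.

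**Step 4: power at the numbers that the article implies.** 54 × 0.8 = 43.2 and 50 × 0.8 = 40.

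| Enrolled | Loss | Evaluable | λ = 0.25 N | Power |
|---|---|---|---|---|
| 54 | none | 54 | 13.50 | 0.950 |
| 54 | 20% | 43 | 10.75 | 0.893 |
| 50 | none | 50 | 12.50 | 0.934 |
| 50 | 20% | 40 | 10.00 | 0.869 |
| 68 | 20% | 54 | 13.50 | 0.950 |

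Rounding 43.2 up to 44 gives 0.900.

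**Step 5: what f = 0.25 means under each test.** Let σ be the SD at one time point. The SD of change is σ√(2(1 − ρ)) = σ√(2 × 0.5) = σ.

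- *Group-by-time test.* The interaction shifts each of the four cell means by ±0.25σ, so the groups differ in mean change by 4 × 0.25σ = 1.0σ. As a check, a two-sample t-test on change with difference 1.0 SD and 27 per arm has squared noncentrality 1.0² × (27 × 27)/54 = 13.5, the same λ, and power 0.950. With 43 completers, 80% power needs f of about 0.219, that is, a difference of 4 × 0.219 = about 0.88 SD.
- *Time test.* Each time-point mean lies ±0.25σ from the overall mean, so f = 0.25 is an average change of 2 × 0.25σ = 0.5σ over both groups combined.

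**The case against.** The strongest points on the other side are these.

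1. **The design is not badly underpowered on its own terms.** At f = 0.25, power after the full 20% loss is still 0.87 to 0.89, and recruiting 50 with no loss costs under two percentage points. This stands, and it limits the severity.
2. **More participants can be added.** Risk factors 1 and 2 allow extra or replacement participants. Both are optional and fix no number, so they are not a loss allowance. They do mean that 40 completers is a scenario and not a certain outcome.
3. **A different number of measurements could come close.** With three measurements, λ = 0.375 N on 2 and 2(N − 2) degrees of freedom, and 0.95 is first reached at 43, or 44 with equal arms. After 20% loss that is 54 (43/0.8 = 53.75) or 55 (44/0.8). This might explain how 54 arose. It does not rescue the text: the section states two measurements, the analysis uses pre and post, and the Outcomes section has four assessments (baseline, 3, 6 and 12 months). Four measurements would need 36, or 45 after loss.
4. **The meaning of f = 0.25 is not settled.** A reader might infer that the power can only refer to a 1.0 SD difference between the groups, and that this is implausibly large for two active physiotherapies. The article supports neither step. The time test gives the same 54, and the test used is not named. No outcome has a stated expected difference, SD or smallest important difference against which to judge 1.0 SD. The 1.0 SD reading holds only if the calculation was for the interaction.

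**Conclusion.** Wrong as written; it should be fixed but is not critical. The statement that 54 allows for 20% loss contradicts the inputs listed beside it: they give exactly 54 with no loss, whichever of the two tests that reproduce the figure was used. The recruitment figure of 50 contradicts the 54 in the abstract and the sample size section.

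If the 20% loss occurs, the type II error rises from 5% to about 11% (54 enrolled) or 13% (50 enrolled). Most of the shortfall comes from the missing loss allowance; the drop from 54 to 50 alone adds little. These figures rest on the article's own f = 0.25 and ρ = 0.5, on alpha of 0.05 for a single test, and on analysis of completers only. A reader might go further and call the trial inadequate in size, but the article gives no target difference that would show this.

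**What to change.** - In Power and sample size, state that 54 is the number of evaluable participants, and that 20% loss from 54 enrolled leaves 43 and reduces power to about 0.89 at f = 0.25. Remove the claim that the loss is already included.
- Use one recruitment figure in the abstract, Participants, Power and sample size, and Risk factor 1: either 54, or 50 with its power of about 0.87 after loss.
- Name the test to which the power refers. The hypothesis (more improvement with reflex locomotion than with Bobath) is answered by the group-by-time interaction. If that is the test, add that f = 0.25 is a 1.0 SD between-group difference in change, and that 43 completers detect about 0.88 SD at 80% power.

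This costs wording only, and the stated power becomes less favourable. If 0.95 after loss is really intended, the enrolment figure is 68, which is 14 more than the 54 now stated.
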